**Figure 1 FIG1:**
[figure not shown]
Consolidated Standards of Reporting Trials (CONSORT) flow diagram of the study T0 - baseline; T1 - at the perception of intervention (eight weeks); T2 - six months following the intervention

**Table 1 TAB1:** Standard Protocol Items: Recommendations for Interventional Trials (SPIRIT) HADS,- Hospital Anxiety and Depression Scale; OHQ - Oxford Happiness Questionnaire; ECG - electrocardiograph; HRV - heart rate variability; RR - respiratory rate; GSR - galvanic skin resistance; EMG - electromyography; TUG - Time Up and Go Test; 30CST - 30-second Chair Stand Test; MSPSS - Multidimensional Scale of Perceived Social Support; HWS - Holistic Well-being Scale; VisQoL - Vision Quality of Life Index; PSQI - Pittsburgh Sleep Quality Index; T0 - baseline; T1 - at the completion of intervention (eight weeks); T2 - six months following the intervention

	Enrolment	Allocation	Post-allocation			
Timepoint	0	0	T0	Intervention	T1	T2
Enrolment						
Eligibility screen	X					
Ophthalmology test		X				
Oral Informed consent with fingerprint	X					
Allocation		X				
Interventions						
Mindfulness-based yoga				X		
Physical exercise				X		
Wait-list control				X		
Assessment						
Sociodemographic characteristics			X			
HADS, OHQ, biomarkers, ECG, HRV, RR, GSR, EMG, TUG, 30 CST, MSPSS, HWS, VisQoL, PSQI			X		X	X
Treatment-related Information: adverse events, adherence to assigned treatment			X		X	X
Potential confounders: food			X		X	X

Objectives and hypothesis

The objectives will be as follows: to investigate the effect of mindfulness-based yoga (MY) on 1) psychological well-being, 2) physical well-being, 3) physiological well-being, 4) spiritual well-being, 5) health-related quality of life, and 6) sleep quality in individuals with early moderate-to-severe visual impairment and blindness.

We hypothesize that 1) the MY program will effectively improve psychological well-being, physiological well-being, physical well-being, social well-being, spiritual well-being, vision-related quality of life, and sleep quality in individuals with early VI, and 2) the MY will be superior to PE in improving psychological well-being, physiological well-being, physical well-being, social well-being, spiritual well-being, vision-related quality of life, and sleep quality in individuals with early VI.

Design

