This study is a multi-centered, assessor-masked, three-armed RCT. A convenient sampling method will be adopted for the selection of participants. They will undergo the ophthalmologic visual acuity test for screening. Eligible participants will be randomly assigned to either MY, PE, or wait-list control group through computer software (Randomizer) based on gender, age, and severity of vision loss, in which each group contains the same proportion of the factors mentioned above.

The intervention will be for eight weeks (one hour/day, five days a week), and a follow-up assessment will be carried out six months after the completion of the intervention. The study contains three times evaluations in which the baseline assessment (T0) will be before group division. Post-intervention assessment (T1) will be at the end of the intervention for eight weeks. Follow-up assessment (T2) will be six months after the completion of the intervention. The principal researcher will make unannounced weekly visits to the intervener's class to assess the adherence, consistency, and quality of the intervention. In each classroom, MY or PE, two teaching assistants will support the main instructor in conducting the classes to minimize the risk of injury, such as ankle and knee injuries for the participants.

Randomization method

Stratified randomization will be employed to randomly assign participants based on three factors: age, gender, and the severity of visual impairment. This approach aims to reduce potential confounding effects and enhance the validity of the results.

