Given the attrition and missing data in the experiment, the research team will account for a 20% attrition rate and closely monitor the progress of the trial with the aim in mind. To minimize attrition and missing data, it will be emphasized to both research team members and participants that full and complete participation in the intervention is crucial, regardless of the treatment assignment. Follow-ups will be scheduled at participants' convenience, with the assistance of two NGOs, and participants will receive WhatsApp reminders one day before each event.

To handle missing data, we will implement diligent monitoring and provide thorough explanations of study procedures to ensure a positive research experience. Highlighting the altruistic reasons for participation, we will elucidate the significance of maintaining involvement for all the participants. At the end of each follow-up, assessors will explain performance assessments and relevant health concerns to participants [86]. To achieve it, the research team will keenly supervise the whole procedure. The research team will contact participants through the authorities of the two NGOs for follow-up arrangements and conduct follow-up data collection at the participants' convenience.

Additionally, we will identify potential confounding factors and implement controls to mitigate their impact on the study results. This may include adjusting for baseline characteristics, using stratified randomization, and employing statistical techniques such as multivariable regression analysis to control for these factors in the data analysis.

Ethical consideration

This study trial has obtained approval from the institutional ethics committee (IEC) with the Institutional Ethics Committee Clearance Certificate Reference Number: RES/IEC-SVYASA/203/2021. It has been registered in the Clinical Trial Registration of India (CTRI) with the registration number of WHO The Clinical Trials Registry - India: CTRI/2021/08/035853.

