## Results

Data will be collected and extracted using the standard procedure. The appropriate statistical test will be conducted to analyze the above-mentioned variables using SPSS V. 22.0 software (IBM Inc., Armonk, New York). To find out the differences between groups, an ANOVA test will be adopted; to check within-group changes, a repeated measures ANOVA will be used. The findings will be released subsequent to the study of the data.

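### The plan labels food at T0, T1 and T2 a potential confounder and leaves open regression on confounders without limiting it to values from before allocation

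*Protocol article*

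**What the plan says.** Four places in the protocol article bear on this.

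- **Table 1 (SPIRIT schedule).** The row "Potential confounders: food" is marked at all three assessments. The table note defines them: "T0 - baseline; T1 - at the completion of intervention (eight weeks); T2 - six months following the intervention". Food is the only variable that the schedule labels this way.
- **Attrition and missing data.** The team states that "we will identify potential confounding factors and implement controls to mitigate their impact on the study results". The next sentence is permissive: "This may include adjusting for baseline characteristics, using stratified randomization", and then "employing statistical techniques such as multivariable regression analysis to control for these factors in the data analysis". Food is not named here, and no time point is attached to any factor.
- **Design.** The text states that "the baseline assessment (T0) will be before group division".
- **Results.** "To find out the differences between groups, an ANOVA test will be adopted". Repeated measures ANOVA is kept for changes within groups. No covariate is named for either analysis.

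**The concern.** Randomisation makes the arms comparable, apart from chance, on everything fixed before allocation. A variable measured after eight weeks of yoga or exercise, or six months later, is not protected in this way. If the interventions alter what participants eat, food at T1 or T2 is partly a result of the arm. Conditioning on it removes any part of the effect that acts through diet. If an unmeasured trait influences both diet and mood, conditioning on food also makes the arms differ on that trait, even where diet has no effect on mood.

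Calling T1 and T2 food a confounder is therefore a misclassification in the printed plan. The label matters because the analysis text permits regression on whatever carries it. At stake are the contrasts on the primary outcome (HADS) and on the other outcomes. Meanwhile, the covariates that could safely add precision, namely the T0 value and the stratification factors, do not appear in the stated between-group test.

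**Working it through.** The plan gives no figure on this point, so there is none to reproduce. The check is textual, followed by an illustration under assumed values.

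**Reading the sections together**

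1. Table 1 and the section on attrition and missing data use the same term, potential confounders. The only variable that the schedule gives that label is food.
2. The attrition section lists regression as a separate item from adjustment for baseline characteristics. The regression option is therefore not confined to baseline values by its wording.
3. T1 and T2 follow allocation. T0 precedes it according to Design, so T0 food is an ordinary baseline covariate. Table 1 as printed sets the T0 column after allocation, which conflicts with Design and needs reconciling.
4. The Results section names ANOVA without covariates. It neither uses nor withdraws the regression option.

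So the plan permits adjustment for T1 or T2 food but does not prescribe it.

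**Illustration of the mechanism (all values assumed)**

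Let A be the arm (0 or 1), U an unmeasured trait with variance 1, and e standard normal noise, independent in each equation.

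- Food after allocation: M = a·A + 0.6·U + 0.8·e
- Outcome: Y = 0.4·A + b·M + g·U + e

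The unadjusted difference estimates the total effect, 0.4 + a·b. Within arm, the slope of U on M is 0.6 / (0.6² + 0.8²) = 0.6. The slope of Y on M is therefore b + 0.6·g, and the arm coefficient adjusted for M is (0.4 + a·b) − a·(b + 0.6·g) = 0.4 − 0.6·a·g.

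A simulation with 400,000 subjects in two arms agrees:

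| a | b | g | Total, formula | Unadjusted, simulated | Adjusted, formula | Adjusted, simulated |
|---|---|---|---|---|---|---|
| 0 | 0.3 | 0.5 | 0.40 | 0.401 | 0.40 | 0.401 |
| 0.2 | 0.3 | 0 | 0.46 | 0.460 | 0.40 | 0.400 |
| 0.5 | 0.3 | 0 | 0.55 | 0.556 | 0.40 | 0.405 |
| 0.2 | 0 | 0.5 | 0.40 | 0.401 | 0.34 | 0.341 |
| 0.5 | 0 | 0.5 | 0.40 | 0.403 | 0.25 | 0.254 |

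- Row 1: the arm does not change food, so adjustment does no harm.
- Rows 2 and 3: adjustment removes the part of the effect that acts through food.
- Rows 4 and 5: food has no effect on the outcome, yet the adjusted estimate falls below the true 0.40. With g of the opposite sign it would rise above it.

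The 0.4 is a convenient input in units of the noise SD. It is not taken from the sample-size section, whose effect size of 0.4 is given without a metric.

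**The case against.** A reader might infer that the plan will adjust the randomised comparison for food at T1 and T2. The documents do not support that. The attrition section says only what the controls may include, its first-named option is baseline adjustment, and it does not mention food. Table 1 is a collection schedule, not a model. The stated between-group analysis has no covariates. Recording food at T1 and T2 for descriptive use fits the present text.

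A reader might also infer that covariates will be chosen after the data are seen. The text says that factors will be identified, but not when or from what, so that inference fails too.

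Three further points weigh against the concern. The Limitations section mentions food habits only as something the centres share, and relies on stratified randomisation. The Adherence section asks participants to keep their daily routine, which may limit dietary change. Covariate lists often sit in an analysis plan, and none is shown here.

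Most of this stands, and it limits how strongly the point can be put. It does not remove it. Similar food habits across centres say nothing about dietary change between arms within a centre. And the point does not rest on a missing covariate list: it rests on what is printed, namely a confounder label on post-allocation measurements and a permission for regression that does not exclude them.

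**Conclusion.** The point holds as a permission that the plan leaves open, not as an error that it commits to. Bias would arise only if T1 or T2 food entered the between-arm model and the interventions changed diet. The documents support neither condition with data, so the size cannot be estimated. The illustration shows the mechanism under assumed inputs and predicts nothing for this trial.

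It is still worth acting on. The label is wrong for T1 and T2 food in a randomised comparison, and a better analysis is available from variables already scheduled. Adjusting for the T0 outcome and the stratification factors keeps the comparison within what randomisation protects, and it gains precision to the extent that they predict the outcome.

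**What to change.** Amend the confounding paragraph under attrition and missing data, and the Results section, to say that:

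- the between-arm comparison at T1 and at T2 adjusts only for prespecified variables fixed before allocation: the T0 value of the outcome, age group, gender and severity of visual impairment. Centre and T0 food enter only if named in advance;
- no variable measured after allocation is a covariate in that comparison;
- food at T1 and T2 is reported descriptively by arm. Any question about diet as a mechanism is a separate mediation analysis, labelled as such.

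In Table 1, drop the confounder label from food at T1 and T2, and reconcile the position of T0 with Design, since the T0 values qualify as pre-allocation only if Design is right.

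The cost is a few sentences and one table edit. The T0 outcomes and food are already scheduled, and the stratification factors are needed for allocation anyway, so no new data are required. The abstract reports data collection as ongoing, which leaves room to make the change before analysis.

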## Results

Data will be collected and extracted using the standard procedure. The appropriate statistical test will be conducted to analyze the above-mentioned variables using SPSS V. 22.0 software (IBM Inc., Armonk, New York). To find out the differences between groups, an ANOVA test will be adopted; to check within-group changes, a repeated measures ANOVA will be used. The findings will be released subsequent to the study of the data.

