## Abstract

Background

People with visual impairment (VI) tend to face more psychological distress than normally sighted individuals due to mobility restrictions, fear of falling, and sleep disturbances. However, research to address these problems is rare. This study aims to investigate the effect of mindfulness-based yoga versus physical exercise on the psychological well-being of individuals with VI.

Methods

This study will be a single-blinded, three-armed, multicentered, randomized controlled trial (RCT). A total of 132 participants with VI (ages 15-25) will be recruited in the study and will be randomly assigned to either group 1 (mindfulness-based yoga), group 2 (physical exercise), or group 3 (wait-list control). Groups 1 and 2 will receive intervention for 40 hours (eight weeks, weekly five days, one hour/day), whereas group 3 will continue their daily activities as usual. The intervention will take place in the afternoon from Monday to Friday. The timing varies between 4-5 pm according to the different time schedules of the institutions of the blind. Three times, assessments will be conducted at T0 (baseline), T1 (eighth week at the completion of the intervention), and T2 (sixth month following the completion of the intervention). ANOVA will be used to find out the differences between groups; repeated measures ANOVA will be used to check within-group changes.

Trial status

The study was first screened in December 2021. The recruitment of participants has been completed in two centers covering 62 individuals with VI, and intervention started in August 2022. The data collection is still ongoing due to the nature of the study design, a specific demographic, complex logistics, and administrative bottlenecks. The study incorporates three different groups and a substantial sample size (n=132). The specific demographic, people with visual impairments, are rare and difficult to locate. In addition, a six-month follow-up assessment contributes to complex procedures while coordinating between various institutions and securing necessary authorizations.

Discussion

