However, PE primarily focuses on physical movement and aims at performance, fitness, and skill development. The teaching technique of PE typically is conducted with dynamism and incorporates repetitive movements, drills, and activities without any mindful awareness of breath regulation or meditation. Exercises in the PE group are usually fast-paced and dynamic, with the main goal of developing physical strength, stamina, and agility through organized physical exercises, though the intensity in this study is under control for safety and research purposes [47].

Group 3: Wait-List Control Group

Participants in the wait-list control group will continue their daily routine without receiving either MY or PE training. Three measurements will be taken at T0, T1, and T2 to compare with the other two groups. After the study period, the same MY or PE protocol will be given according to the participants' interests. The participants originally assigned to the PE group will receive MY sessions, whereas those in the yoga group will switch to the PE group. Participants in the wait-list control group can choose either class based on their personal preference after the completion of the intervention.

Blinding

This study is a single-blind RCT. In this study, outcome assessors, who are responsible for outcome measurement, will be blinded to group allocation of the participants. However, it would be hard to blind the participants given the nature of the intervention. Typically, in other research, participants would be informed of their group allocation using an opaque envelope to ensure blinding. However, given that the participants in this study are visually impaired, the opacity of the envelope is irrelevant. The single-blind design may potentially expose the study to risk of bias regarding the outcome expectations of the participants, attrition rate, response rate, and willingness to accept randomization.

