The strengths of this research are: 1) subjective psychological questionnaires correlating with objective, evidence-based assessment will strengthen the study design; 2) multiple centers with a large sample size in different geographical areas will support generating the findings of this research; and 3) a three-group study design will enhance the strength of the study. The active control group (PE group) will be compared with the experimental group (MY group) to discover the potential mechanisms of yoga, especially the effects of mindful awareness on psychological well-being. The wait-list control group will be compared with the other two to reveal the significance of either type of physical activity contributing to general well-being.

Limitations

Potential limitations and their related strategies need to be acknowledged. Subject dishonesty might happen during the interview process to protect one's privacy and social identification, as they might appear to have prosocial behaviors toward interviewers. To ameliorate the effects of bias, the interviewers will inform the participants that private information will be kept confidential, and the interview will be in the form of a one-on-one session. It is crucial to keep in mind that despite the study's design using numerous centers and a sizable sample size from various geographic regions, regional-specific factors like cultural differences, resource accessibility, and customs may still have an impact on the findings. However, in this study, stratified randomization will be adopted to minimize the potential effects of confounding factors such as location, population, educational and cultural differences where the research will take place. Since each center shares certain similarities in terms of setting, such as food habits, living standards, teaching methods, and cultural background, it is reasonable to expect that various confounding factors will have the minimum effects on the results. Additionally, this study will investigate the evaluation and implementation of the MY or PE protocol. However, social support will not be considered as one factor for randomization. Therefore, it will be possible if there will be varying levels of social support among the three groups. Dropouts and missing data may also pose a risk to internal validity. The strategy to reduce the dropout rate has been discussed previously in the section named "attrition and missing data".

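### Hypothesis 1 names no comparator, and the planned within-group repeated-measures ANOVA is not limited to description; tie the hypothesis to a randomised MY versus wait-list contrast

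*Protocol article*

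**What the plan says.** All references are to the protocol article.

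- **Objectives and hypothesis.** The first hypothesis is that "the MY program will effectively improve psychological well-being, physiological well-being, physical well-being" and further domains; no comparator is given. The second does give one: "the MY will be superior to PE in improving psychological well-being".
- **Results.** Two analyses are named. The first is between arms: "To find out the differences between groups, an ANOVA test will be adopted". The second follows in the same sentence: "to check within-group changes, a repeated measures ANOVA will be used". The Abstract repeats the pair ("repeated measures ANOVA will be used to check within-group changes"). The section states no time point, use of baseline or arm-by-time term, and does not say which analysis decides which hypothesis.
- **Group 3: Wait-List Control Group.** The role of this arm is described so: "Three measurements will be taken at T0, T1, and T2 to compare with the other two groups".
- **Strengths (Discussion).** "The wait-list control group will be compared with the other two to reveal the significance of either type of physical activity". This sentence concerns physical activity of either type and is not linked to hypothesis 1.
- **Design.** "The intervention will be for eight weeks (one hour/day, five days a week"; T2 follows six months after the intervention ends, so T0 to T2 spans about eight months.

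**The concern.** Read alone, hypothesis 1 is a statement about change in the MY arm, and the plan supplies a significance test of exactly that. The test asks whether the mean in one arm differs across T0, T1 and T2. It cannot separate an effect of MY from anything else that moves scores over eight months.

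The article itself describes possible sources of such movement. Participants are students in institutions. They are interviewed orally, one to one, at every visit. Under Attrition and missing data, assessors explain results and health concerns to participants at the end of each follow-up. Under Limitations, some socially desirable answering is expected. All of this can act equally in the three arms.

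If the between-arm comparison showed no difference, a significant before-after change in MY would still be available as apparent support for hypothesis 1. The Discussion foresees integrating the programme into education or rehabilitation if it is found effective, so what counts as effective should be a randomised contrast.

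**Working it through.** The article gives no figure for this point, so there is none to reproduce. The check asks how often each type of test is significant when MY has no effect.

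**Inputs**
- n = 36 per arm: Sample size section, the number before the attrition allowance.
- k = 3 visits (T0, T1, T2): Design section.
- 5% level: Sample size section.
- Assumed, because the article does not give them: the same mean shift *d* from T0 to both T1 and T2 in every arm, with *d* = 0.2, 0.3 or 0.4 SD; the same correlation ρ between any two visits, with ρ = 0.5 or 0.7; normal data; no treatment effect.

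**Within-arm repeated-measures ANOVA in MY**
- Visit means are 0, *d*, *d*. Their sum of squares about the mean is 2*d*² − (2*d*)²/3 = 2*d*²/3.
- The residual variance is 1 − ρ (in SD² units).
- The noncentrality is λ = n × (2*d*²/3) / (1 − ρ), with k − 1 = 2 and (n − 1)(k − 1) = 35 × 2 = 70 degrees of freedom. The 5% critical value of F is 3.13.
- Example at *d* = 0.2, ρ = 0.5: λ = 36 × 0.02667 / 0.5 = 1.92, rejection 21%.
- Example at *d* = 0.4, ρ = 0.7: λ = 36 × 0.10667 / 0.3 = 12.8, rejection 89%.

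| ρ | *d* (SD) | λ | MY arm significant, by formula | MY arm significant, simulated | Three-arm ANOVA on T1 − T0 change, simulated |
|---|---|---|---|---|---|
| 0.5 | 0.2 | 1.92 | 21% | 21% | 5.0% |
| 0.5 | 0.3 | 4.32 | 43% | 44% | 5.1% |
| 0.5 | 0.4 | 7.68 | 68% | 68% | 4.5% |
| 0.7 | 0.2 | 3.20 | 33% | 32% | 5.4% |
| 0.7 | 0.3 | 7.20 | 65% | 66% | 5.2% |
| 0.7 | 0.4 | 12.80 | 89% | 89% | 4.8% |

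The simulation used 3,000 trials per row, so its error is at most about √(0.5 × 0.5 / 3000) = 0.9 percentage points. With no drift, the within-arm test rejected in 5.8% (ρ = 0.5) and 4.9% (ρ = 0.7) of trials, so the test itself behaves properly; the excess comes from the drift.

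**Between-arm test.** With equal drift, the expected difference in change between any two arms is *d* − *d* = 0, so the test keeps its 5% level. An ANOVA of the T1 values alone also stayed at 4.4% to 5.4% in these six settings.

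**The case against.** The strongest reply is that the between-group ANOVA comes first in the same sentence, and that two other sections foresee comparison with the wait-list. Since hypothesis 2 takes PE, the natural comparator for hypothesis 1 is the wait-list. A reader might infer that no controlled analysis is planned; the article plainly says otherwise, and this part of the reply stands.

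A reader might also infer that the trial will rest its efficacy claim on before-after evidence, or will argue that MY changed significantly while the wait-list did not. No section says so. The stated purpose of the repeated-measures ANOVA is only to check change within groups, and the link from it to hypothesis 1 is an inference from the wording.

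Three further points stand in part.
- The article does not say whether the repeated-measures ANOVA is fitted separately in each arm. That is the likelier reading, and the calculation depends on it.
- The rates are conditional on an assumed drift. They show that a within-arm test detects real mean change, and become false-positive rates for efficacy only if that change is read as an effect of MY.
- A condensed article may leave model terms and the mapping of tests to hypotheses to an analysis plan not shown.

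The last point does not dispose of the matter. The article goes beyond silence: it commits to an uncontrolled significance test beside a hypothesis with no comparator, and an analysis plan consistent with it would carry both forward.

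**Conclusion.** The point holds as a weakness in what is stated. A controlled comparison is planned but not attached to hypothesis 1, and the within-group test is not confined to description. If its result were taken as support for hypothesis 1, the chance of a significant result without any treatment effect would be about 21% to 89% rather than 5%. This assumes a shared drift of 0.2 to 0.4 SD, visit correlation of 0.5 to 0.7, 36 per arm and separate fitting by arm. The exact rates depend on these assumptions; the direction does not, since any shared drift raises the within-arm rate and leaves the between-arm rate at its nominal level.

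The range should not be read as the error rate of the trial as planned, because the article does not make the within-arm result decisive. Severity: should-fix.

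**What to change.** 1. Restate hypothesis 1 as MY versus wait-list.
2. Test it, and MY versus PE for hypothesis 2, in one model of all arms and visits, using arm-by-time contrasts (difference in change from T0) at T1 and then at T2. A baseline-adjusted ANCOVA at each visit is an acceptable alternative.
3. Report within-arm change only as estimates with confidence intervals, labelled descriptive and not evidence of efficacy.

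The cost is a dated amendment, since the trial is registered and under way, and slightly more analysis work. The data and the software stay the same. The article reports data collection as still ongoing, so at that stage the change can be made before the analysis.
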